### Procedure

Participants will be recruited through different online and offline strategies to encourage citizens’ participation according to different cultural backgrounds. This approach ensures inclusivity and reflects the diverse population we aim to engage in the study. Offline recruitment includes in-person interactions with community members called “key figures”, video promotion, presentations and personally addressing people in public areas. Online recruitment efforts will include websites, social media networks, and local newspapers. By utilizing both digital and physical recruitment strategies, we aim to maximize reach and engagement. Interested individuals can enroll by initiating an application procedure through the study’s website [20], where they will complete an application form to assess eligibility. Eligible participants will then be invited to create a secure personal account and will be provided with a digital patient information form (PIF) and a digital informed consent (IC) form (see Additional file 1). The IC procedure is conducted digitally using Valid Sign, a digital signature platform that enables secure signing of documents online and streamlines the consent process. In line with our aim of ensuring simplicity and accessibility, an invitation email will provide instructions on downloading the Your Research CTMS application to their tablet or smartphone. This application will serve as the primary platform for all study related activities. Results will be sent directly to the server and will be accessible to participants at any time through the app. There will be a variety of platforms provided for additional inquiries about the study procedures including mail, WhatsApp or phone calls. Participants who complete and return the signed e-consent form will be enrolled and randomized in the trial. Depending on their assigned intervention arm, participants will be required to fill in questionnaires, sent via the Your Research app, within two weeks. To ensure adherence, push notifications will be sent to participants who do not complete the questionnaire within 3 days. Participants can choose their preferred notification method, which may include email, SMS, or application notifications. The data collection will run for 24 months. Participants, including those in the control group, will complete the EQ-5D-5L questionnaire via the Your Research CTMS application at baseline (0 months), and at 6, 12, and 24 months. Recruitment will be closely monitored to ensure that the target sample size is achieved. Once the sample size is reached, inclusion will be stopped. Participants will receive compensation at the end of the study based on the number of completed questionnaires, with a maximum of €50 (paid in gift cards). Additional vouchers may be earned by inviting more participants via the app. Participants can withdraw from the study at any time during the trial. To address any logistical or general MDD-related queries, participants can visit the study website [20] or contact the researchers by e-mail or WhatsApp. Additionally, a phone line will be available for inquiries on weekdays, staffed by Erasmus MC MOOD study researchers. To ensure participant safety, the program includes specific measures for addressing potential risks. For example, if questionnaire responses indicate severe depressive symptoms or a risk of self-harm, participants will be immediately directed to appropriate crisis support resources, such as ‘De Luisterlijn’ or ‘113 suicide prevention’ [34]. Additional information on suicide prevention and emergency contacts will be provided as needed, based on the assessment results. These safety measures are crucial for addressing any emerging mental health concerns in real-time, ensuring participant well-being throughout the trail.

The protocol and this manuscript were written following SPIRIT [35] guidelines. A detailed explanation of the screening timeline and intervention components is illustrated in SPIRIT Fig. 1.

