## Methods/design

### Study design and setting

The MOOD (MObile-Based Screening fOr Depression) study is designed as a prospective, randomized controlled multi-arm trial with three parallel groups: a control group and two different intervention groups. We developed the MOOD intervention program by incorporating expertise from various stakeholders, including citizens and experts in mental, digital and public health. After completing a short survey to check for inclusion and exclusion criteria and the digital informed consent procedure, randomization will be performed at the individual level in a 2:1:1: ratio for the control group and the two intervention groups respectively. Participants in the control group will not receive mobile-based screening for MDD, while those in the two intervention groups receive a screening test using the PHQ-9 questionnaire at four-week intervals over a 12-month period. The intervention groups will be divided into two arms. In the one-test referral arm, participants who score positive for moderate to severe depressive symptoms (PHQ-9 score > 10) on a single screening will be referred for further diagnostic evaluation and treatment if necessary. In the multiple-test intervention arm, participants will only be referred for further diagnostic evaluation and treatment after three consecutive positive screenings indicating moderate to severe depressive symptoms (PHQ-9 score > 10). For the screening process in this study, we utilized a Clinical Trial Management System (CTMS) software developed by Your Research [20]. The application enhances efficiency by automating research processes such as data management, workflow optimization, and real-time reporting to ensure consistency and compliance throughout the study. Key features include error reduction, robust data encryption, comprehensive audit trails, ensuring data integrity and regulatory compliance. Participants can use this application at any moment to complete the survey(s). If any questionnaire is not finished after three days, participants will receive a reminder via email or push notification, depending on personal preferences. A second reminder will be sent after ten days. This allows participants to remain engaged and adhere to the study timeline. All study materials, including the website, questionnaires, Patient Information Form (PIF), and Informed Consent (IC) form, will be accessible in six languages: Dutch, English, Turkish, Spanish, Polish, and Arabic and will be provided in B1 language proficiency level. These languages were selected to ensure broad accessibility and inclusivity, reflecting the diverse linguistic backgrounds of the study population. Additionally, the questionnaires themselves will be available in 12 languages to further ensure the validity of the responses across the diverse population. The trial will be conducted by the Department of Public Health at the Erasmus University Medical Center Rotterdam, the Netherlands. The intervention area will focus on Rotterdam, particularly on the Southern part of the city, namely the districts Charlois, Feijenoord, and Ijsselmonde. The population in these districts is ethnically and socioeconomically diverse, with more than 90% having origins outside of Dutch heritage and more than 20% is unemployed [21]. It is expected that in this region there will be an above average prevalence of MDD, which will increase the screening’s potential impact and allow for better measurement [1, 6, 19]. This study is evaluated and approved by the Central Committee on Research Involving Human Subjects (CCMO) of the Netherlands (reference: # NL84280.078.23). The study is registered at the ClinicalTrials.gov Protocol Registration and Results System (ID = NCT05989412).

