
### Participants

We aim to include 1786 participants. Inclusion criteria are (1) be at least 18 years old; (2) live in the municipality of Rotterdam; (3) have access to a computer or smartphone; and (4) being able to complete the questionnaires in one of the provided languages. Exclusion criteria are (1) currently receiving therapy from a psychologist or psychiatrist for depressive symptoms; or (2) having been referred to a psychologist or psychiatrist in the past year for depressive symptoms. Eligibility screening will be conducted through the study’s website, after which participants will digitally sign the consent form via email. This will be followed by a baseline assessment completed through the application.

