### Randomization

Randomization will be performed by the Your Research CTMS software application as block randomization with a 2:1:1 allocation using stratification for age, gender, and living area. Due to the nature of the intervention neither participants nor staff can be blinded to allocation after randomization. A case report form for each participant will be prepared and labeled only with the participant number. A consent and identification list with numbers will be stored by Your Research. The two intervention groups will remain coded throughout the analysis phase.

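### Randomisation is triggered by e-consent, and nothing requires the self-reported baseline EQ-5D-5L to be completed before allocation or its disclosure in this unblinded trial

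*Protocol article*

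**What the plan says.** Three sections of the protocol article describe the route into the trial.

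- **Study design and setting:** "After completing a short survey to check for inclusion and exclusion criteria and the digital informed consent procedure, randomization will be performed". No baseline measurement is listed before allocation.
- **Procedure:** "Participants who complete and return the signed e-consent form will be enrolled and randomized in the trial". The next sentence reads: "Depending on their assigned intervention arm, participants will be required to fill in questionnaires, sent via the Your Research app, within two weeks". A little later, participants in all arms "will complete the EQ-5D-5L questionnaire via the Your Research CTMS application at baseline (0 months), and at 6, 12, and 24 months".
- **Participants:** after eligibility screening and the digital consent signature, "This will be followed by a baseline assessment completed through the application". Randomisation is not mentioned here.

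The Randomization section stratifies by age, gender and living area, so a baseline EQ-5D-5L is not needed in order to allocate. It also states: "Due to the nature of the intervention neither participants nor staff can be blinded to allocation after randomization".

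The primary outcome is the EQ-5D-5L difference from baseline to 12 months, control against the combined intervention groups. It is analysed by linear regression correcting for baseline. The Sample Size section relies on the same baseline, through an assumed correlation of 0.8 and a design effect of 0.36.

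**The concern.** A baseline used for adjustment should not be open to influence from treatment assignment. Here it is a self-report, one of its five dimensions is anxiety/depression, and allocation cannot be concealed once made. If people can complete it after learning their arm, their answers may reflect that knowledge. The adjusted comparison then removes part of a difference that allocation itself created, and the treatment estimate is biased.

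The target effect is only 0.016, so a small shift matters. The design also depends on this covariate: without baseline adjustment the planned numbers are far too small.

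A second consequence concerns who is analysed. If allocation comes first, some randomised participants may never complete a baseline. They would be lost after randomisation and would not enter a regression that requires a baseline value, unless the analysis handles them in some other way.

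**Working it through.** **1. Order of steps, section by section**

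| Section | Stated before randomisation | Place of the baseline |
|---|---|---|
| Study design and setting | Eligibility survey, e-consent | Not mentioned |
| Procedure | Return of signed e-consent | EQ-5D-5L at 0 months, introduced after the sentences on randomisation and arm-dependent questionnaires |
| Participants | Randomisation not mentioned | After consent |

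No section makes baseline completion a condition of allocation or of disclosure.

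**2. Reproducing the plan's sample size**

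Inputs from Sample Size: effect 0.10 × 0.40 × 0.40 = 0.016; SD 0.18; correlation 0.8; 5% significance level (two-sided assumed); 80% power.

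- Design effect: 1 − 0.8² = 0.36.
- Residual SD: 0.18 × √0.36 = 0.108.
- n per group = 2 × (1.960 + 0.842)² × 0.108² / 0.016² ≈ 716, against 714 stated. Power at 714 is 79.9%.
- With 20% loss: 714 / 0.8 = 892.5, so 893 per group and 1,786 in total, as stated.

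**3. How much rests on the baseline**

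With SD 0.18 and no adjustment, n is 1,987 per group (2,484 after 20% loss). At 714 per group, power without adjustment is 39.0%.

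**4. Bias from a baseline shift**

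Let b be the shift in mean baseline, intervention minus control, caused by allocation, on the scale used in Sample Size with higher meaning better QoL. Assume equal SDs at baseline and 12 months, and no carry-over of the reaction to 12 months.

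- Adjustment slope = 0.8 × (0.18 / 0.18) = 0.8.
- Bias in the adjusted effect = −0.8 × b. It is the same whether the dependent variable is the 12-month score or the change, because baseline is in the model.
- Standard error at 714 per group = 0.108 × √(2 / 714) = 0.00572.

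The documents give no value for b, so the range below is an assumption.

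| Assumed size of b | Size of bias | Share of 0.016 | Two-sided type I error | Power if intervention baseline is raised |
|---|---|---|---|---|
| 0.002 | 0.0016 | 10% | 5.9% | 71.2% |
| 0.005 | 0.004 | 25% | 10.8% | 55.5% |
| 0.010 | 0.008 | 50% | 28.8% | 28.8% |

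The last two entries of the bottom row agree because an apparent effect of 0.008 arises in both: 0 + 0.008 under no effect, and 0.016 − 0.008 under the target effect. A shift that lowers the intervention baseline biases in the intervention's favour instead.

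**5. Effect of the fix on sample size**

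Moving the baseline before allocation changes none of the inputs in step 2, so the recruitment target stays at 1,786.

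**The case against.** The strongest reply is that the order is inferred. A reader might conclude that the baseline is collected after randomisation, by people who already know their arm, and perhaps after a first PHQ-9 with its result. The documents do not establish any of this.

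- Saying that randomisation comes after consent does not exclude a baseline in between, and the Participants section fits either order.
- The sentence on arm-dependent questionnaires may mean only the PHQ-9 screening, since the EQ-5D-5L is common to all arms and is described separately.
- The Randomization section does not say when the arm is disclosed, and no section orders the PHQ-9 against the EQ-5D-5L.
- The SPIRIT timeline (Fig. 1), which might settle the matter, is not available in the text reviewed.
- Stratifying by gender, which is not an eligibility criterion, means some further information is collected before allocation. The condensed text therefore leaves steps out, although the application form could supply this item.

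All of that stands, and it limits the point to what the text fails to secure. It does not remove it: two sections name consent as the step leading to randomisation, and none protects the baseline.

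The bias figures are also fairly challenged. The size and direction of b are unknown, and a reaction lasting to 12 months would change the net bias. If it persisted in full, the adjusted estimate would move by b − 0.8b = 0.2b. The table is a sensitivity range and predicts nothing.

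Finally, it is too strong to say that people without a baseline cannot be analysed. The article plans mixed models for missed questionnaire rounds, and a mixed model that treats baseline as an outcome can keep them. The primary analysis is nevertheless described as a linear regression correcting for baseline, and no mixed model undoes a baseline that allocation has already influenced.

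**Conclusion.** The point holds in this form: as written, the article randomises on return of the e-consent and does not require the baseline EQ-5D-5L to precede allocation or its disclosure. The most natural reading is that the baseline can be completed after allocation in an unblinded trial. That it is in fact completed then, or by participants who know their arm, is not shown.

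If allocation shifted the baseline by b, the primary estimate would be biased by about −0.8b. For assumed shifts of 0.002 to 0.010, that is 10% to 50% of the 0.016 effect. This rests on equal SDs, the article's own correlation of 0.8 and no carry-over to 12 months; direction is unknown. Participants randomised without a baseline would also leave the primary regression unless other handling is specified.

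The order deserves settling now because a later analysis plan cannot move a measurement to before randomisation.

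**What to change.** Set one order in Study design and setting, Participants and Procedure:

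1. e-consent;
2. baseline EQ-5D-5L and demographics completed in the app;
3. randomisation triggered by submission of the baseline;
4. disclosure of the arm, then the first PHQ-9 in the screening arms.

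If the app already works this way, correct Study design and setting and Procedure to say so; that closes the point.

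The cost is protocol wording and, if needed, a workflow setting in the trial app. The small downside is that consenters who never complete the baseline are not randomised, so they are lost before allocation and not after it.

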**Fig. 1 Fig1:**
[figure not shown]
SPIRIT figure. A cross indicates one-time (screening) measurement. A bold line represents a 4-weekly screening measurement. *Patient information form/Informed consent. **Clinical Trial Management System *** Compensation preference will be assessed during the demographics assessment

### Randomization

Randomization will be performed by the Your Research CTMS software application as block randomization with a 2:1:1 allocation using stratification for age, gender, and living area. Due to the nature of the intervention neither participants nor staff can be blinded to allocation after randomization. A case report form for each participant will be prepared and labeled only with the participant number. A consent and identification list with numbers will be stored by Your Research. The two intervention groups will remain coded throughout the analysis phase.

### Outcomes measures

#### Primary outcome measures

The primary endpoint analysis (12 months) will be a comparison of outcomes in QoL for participants assigned to the control group and the combined intervention groups. The EQ-5D-5L total score differences between the baseline measurement (T0) and the post-intervention measurement at 12 months will be used to evaluate the outcome. This primary outcome measure allows us to broaden the impact of the intervention on participant’s’ overall well-being.

#### Secondary outcome measures

QoL: assessing participants’ QoL at baseline (T0) and post-intervention measurement (T24 months) using EQ-5D-5L total scores. Additionally, the last question of the EQ-5D-5L will be examined separately since it focuses on mental health. The EQ VAS will also be used to capture participants’ self-rated health, providing an additional measure of overall health perception.Symptoms of depression: evaluating the occurrence and severity of MDD symptoms using the nine-item PHQ-9.Screening adherence: the adherence to the screening intervention will be examined by assessing the proportion of participants completing the prescribed tests, aiming to understand the feasibility of the screening strategy.Screening experiences: participants’ experience with the screening strategy will be evaluated through self-reported questionnaires after 6 and 24 months.Population differences: the study will identify differences in MDD symptoms within the population based on social demographic characteristics, including age, gender, ethnicity, education level, living area and financial situation.

### Sample Size

In this study we compare the control group with both combined intervention groups with one-test referral for further diagnosis and treatment, and with multiple-test referral follow-up for further diagnosis and treatment. A total of 1,428 participants are required for the study, utilizing a 2:1:1 randomization scheme. This sample size will provide 80% power to detect a difference corresponding to an improvement of 0.40 in QoL. Additionally, frequent screening is expected to be effective in 40% of participants diagnosed with MDD, with a significance level set at 5% [30, 36–38]. Furthermore, a cumulative incidence of MDD during 12 months of 10% was assumed in our high-risk population [27, 39, 40]. These numbers lead to an expected difference in QoL of 0.016 at 12 months between the screening and control groups. A standard deviation of 0.18 in the score of the EQ-5D-5L in the general population has been expected [30, 41]. In the analysis, adjustments were made for the baseline EQ-5D-5L, assuming a correlation coefficient of 0.8 between the baseline measurement and the measurement at 12 months [42]. The design effect for adjusting for the EQ-5D at baseline is hence 0.36. As a result, calculating the sample size using the design effect for a two-sample t-test indicates that 714 participants are required in the control arm and combined intervention arms. To compensate for the potential 20% loss [43] of follow-up in both arms, we aim to recruit an additional 179 participants for the control arm and 179 participants for the intervention arm (1:1 between both intervention groups). To reach our goal we therefore need to include 1,786 participants in total.

### Data collection and management

Primary and secondary outcome measures for the MOOD trial will be collected using mobile-based questionnaires. Data will be consistently collected and stored securely using encrypted digital files in password-protected folders, accessible only to a limited number of researchers. The secure handling of participant data is central to maintaining confidentiality and integrity throughout the study. Participants will be assigned unique identification numbers for confidentiality. Contact information will be kept separate from other research data gathered throughout the study. Following the study’s completion, all data will be archived safely for 15 years at Erasmus Medical Center. Once all outcome data has been collected, it will be exported to a statistical program. All data will be kept and stored following the Personal Data Protection Act.

### Statistical analysis

At baseline, descriptive statistics will be utilized to describe participant characteristics, including demographic variables. This baseline assessment provides a foundation for understanding the distribution of key characteristics across the study groups. The statistical analysis for QoL at 12 months will use a standard linear regression model, correcting for baseline QoL measurements and other determinants. Multiple-testing correction will be applied, with the primary focus on identifying differences after 12 months between the control group and combined intervention groups. The secondary analysis utilizes a linear mixed model, incorporating interactions between time points and interventions to investigate screening effects over various time points. It assumes similar effects for both interventions, while interaction terms assess potential differences between intervention arms. This allows us to capture the nature of participant’s responses to the intervention over time. No missing values are anticipated for both the EQ-5D-5L and the PHQ-9 due to mandatory completion. However, there is a potential for entire questionnaire rounds to be missed, thereby resulting in missing data. To mitigate the impact of potential missing data, we will address it using mixed models. Included in the analysis are explanatory variables such as age, gender, ethnicity and other relevant factors readily available for consideration. Table 1 provides a summary of methods of analysis for each variable.

**Table 1 Tab1:** Variables, measures and methods of analysis

**Variables/outcome**	**Hypothesis**	**Outcome Measures**	**Methods of Analysis**

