**1) Primary**			
QoL at 12 months	Intervention improves QoL from baseline to 12 months	EQ-5D-5L total score differences from baseline to 12 months	Linear regression, correcting for baseline

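### The primary 12-month regression uses only participants with a 12-month score; the mixed model named as the missing-data remedy is assigned to the secondary analysis

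*Protocol article*

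**What the plan says.** Under Statistical analysis, the primary method is given as: "The statistical analysis for QoL at 12 months will use a standard linear regression model, correcting for baseline QoL measurements and other determinants". The primary row of Table 1 repeats it more briefly: "Linear regression, correcting for baseline".

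The mixed model has a different place: "The secondary analysis utilizes a linear mixed model, incorporating interactions between time points and interventions". Table 1 likewise lists it for the 24-month outcome only.

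On missing data, the same section expects that "there is a potential for entire questionnaire rounds to be missed, thereby resulting in missing data", and continues: "To mitigate the impact of potential missing data, we will address it using mixed models". It does not say which analysis this covers.

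Under Procedure, participants in all arms, controls included, "will complete the EQ-5D-5L questionnaire via the Your Research CTMS application at baseline (0 months), and at 6, 12, and 24 months".

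Randomization specifies "block randomization with a 2:1:1 allocation using stratification for age, gender, and living area". On covariates, Statistical analysis says: "Included in the analysis are explanatory variables such as age, gender, ethnicity and other relevant factors readily available for consideration". Living area is not named there or in Table 1's primary row; in Table 1 it appears only as a subgroup factor.

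Sample Size allows for 20% loss in both arms.

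**The concern.** An ordinary regression of the 12-month score on baseline has no outcome for anyone without a 12-month questionnaire, so it drops them. The one missing-data remedy in the article belongs to another analysis. If the mixed-model sentence was meant to cover the primary endpoint, it contradicts the stated primary method. If it was not, the primary endpoint has no stated remedy.

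The target effect is only 0.016, so modest selection among responders matters. The article itself gives grounds to expect selection that differs by arm. Only the screened arms get 4-weekly questionnaires and possible referral, allocation is unblinded, and payment depends on the number of questionnaires completed. The Discussion also suggests that regular feedback through the app could reduce dropout. The 6-month EQ-5D-5L is the obvious information on people lost later, and the primary test does not use it.

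**Working it through.** **Inputs from Sample Size:** gain of 0.40 per person helped; 40% helped; 10% incidence over 12 months; SD 0.18; baseline to 12-month correlation 0.8; 5% significance (taken as two-sided); 80% power; 20% loss.

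**1. The plan's own figures.**
- Effect: 0.40 × 0.40 × 0.10 = 0.016.
- Adjusted SD: 0.18 × √(1 − 0.8²) = 0.18 × √0.36 = 0.108.
- n per side: 2 × [0.108 × (1.960 + 0.842) / 0.016]² = 715.2, so 716 against the stated 714. This reproduces.
- Loss: 714 / 0.80 = 892.5, so 893 per side and 1,786 in total, which matches. Planned loss is 1,786 − 1,428 = 358.
- Power at 714 per side: 79.9%.

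The 714 is the number left after loss, so the sizing matches a regression on people with a 12-month score.

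**2. Precision from the 6-month score.** The article gives neither a correlation with the 6-month score nor a 6-month completion rate. Both are assumed: correlations of the 6-month score with baseline 0.80 to 0.85 and with the 12-month score 0.80 to 0.90; completion 80 to 100%. With p the partial correlation of the 6- and 12-month scores given baseline, the variance under monotone loss is proportional to (1 − p²)/714 + p²/n6, where n6 = 893 × 6-month completion. The effective n is its inverse.
- Completion 80%: n6 = 714, so effective n = 714 and there is no gain.
- Correlations 0.80 and 0.80, completion 100%: p = 0.16/0.36 = 0.444; effective n = 743; power 81.5%.
- Correlations 0.85 (baseline to 6) and 0.90 (6 to 12), completion 100%: p = 0.22/√(0.2775 × 0.36) = 0.696; effective n = 791; power 83.8%; variance ratio 714/791 = 0.90.

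The variance reduction is therefore 0 to 10%.

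**3. Bias when loss depends on the observed 6-month score.** Simulation with 893 per side, 20% loss in each arm, true effect 0.008 at 6 months (assumed) and 0.016 at 12, a 6-month score for everyone, and 1,500 runs per scenario. Loss is logistic in the 6-month score, with the slope per SD shown; a larger slope means more loss among those with poor scores. Each pair of results is for correlations (baseline to 6, 6 to 12) of (0.80, 0.85) and (0.85, 0.90).

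| Slope, control / screened | Regression on responders | Likelihood with 6-month score |
|---|---|---|
| 0 / 0 | 0.0160, 0.0163 | 0.0160, 0.0163 |
| 0.5 / 0.5 | 0.0160, 0.0163 | 0.0160, 0.0163 |
| 0.7 / 0.3 | 0.0134, 0.0132 | 0.0161, 0.0160 |
| 0.5 / 0 | 0.0125, 0.0120 | 0.0162, 0.0158 |
| 0.3 / 0.7 | 0.0188, 0.0187 | 0.0160, 0.0158 |

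Equal dependence leaves the regression essentially unbiased. Unequal dependence moves it to between 0.0120 and 0.0188, that is −25% to about +17%. For scale, the standard error at 714 per side is 0.108 × √(2/714) = 0.0057. An expected estimate of 0.012 gives 0.012/0.0057 = 2.10, hence power Φ(2.10 − 1.96), about 56% instead of 80%.

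**4. Loss that depends on 12-month depression itself.** Let 10% of controls and 6% of screened participants be 0.40 worse at 12 months. Let depressed controls drop out at 35% and everyone else at 20%.
- Depressed share of control responders: 0.065/0.785 = 0.0828. Estimate: 0.40 × (0.0828 − 0.06) = 0.0091.
- Arms reversed: 0.039/0.791 = 0.0493. Estimate: 0.40 × (0.10 − 0.0493) = 0.0203.

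This is missing not at random. In a large simulation of the first case (baseline to 6-month correlation 0.8, 6- to 12-month correlation 0.8 to 0.85, all 6-month scores observed), the likelihood model gave about 0.009 if no case was already depressed at 6 months, 0.011 if half were, and 0.014 if all were. It removes none, about 30% and about 70% of the bias (for example, (0.014 − 0.0091)/(0.016 − 0.0091) = 0.71).

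**The case against.** Baseline-adjusted regression at a single time point is a standard primary analysis and agrees with the sizing. A mixed model over all time points is already planned, so the trial as a whole does not discard the 6-month data. That the primary test uses responders only is inferred from the method and from the 714 of 893, not stated. Covariance structure, analysis population and imputation details belong to an analysis plan that is not shown. All of this stands, and none of those details is counted against the article. What remains is a conflict in the printed text between the primary method and the missing-data remedy.

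Three stronger readings are tempting but unsupported:
- **That 20% loss by itself biases the primary result.** It does not. Material bias in step 3 needs dependence that differs by arm. The article gives reasons to expect this but no figure, and it assumes the same loss rate in both arms.
- **That the mixed model would turn 0.009 or 0.020 back into 0.016.** Those figures come from loss that depends on the outcome itself, and step 4 shows the model recovers only part of the difference, or none. They motivate a sensitivity analysis and nothing more.
- **That the stratification is ignored and the standard errors are invalid.** The text names age and gender and allows for other determinants. Only living area is unnamed for the primary model, and omitting a stratification factor generally makes standard errors too large, which is conservative.

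**Conclusion.** The point holds as a should-fix. The stated missing-data remedy does not reach the primary endpoint, where 358 of 1,786 participants are expected to be lost, and the 6-month score goes unused in that test. Under assumed arm-differential dependence on the 6-month score, the regression's expected estimate lies between about 0.012 and 0.019 against a true 0.016, and a likelihood analysis using that score removes the bias. With equal dependence there is essentially no bias to remove. The gain in precision is 0 to 10% of variance and is nil if 6-month completion is also 80%. These sizes are illustrative, because the article gives neither the 6-month correlations nor the pattern of loss. The sample size is not in dispute. The covariate issue is minor: living area is not named, and the text and Table 1 differ.

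**What to change.** Choose one of two routes and state it in both the Statistical analysis text and Table 1:
1. Make the month-12 contrast of combined intervention versus control, from the linear mixed model already planned, the primary analysis. Use the baseline, 6- and 12-month EQ-5D-5L for all randomised participants in their assigned arm.
2. Keep the linear regression, with multiple imputation of missing 12-month scores that uses the 6-month score.

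Under either route, name age, gender and living area as fixed covariates alongside baseline, in place of the open-ended list. Add a delta-adjusted sensitivity analysis, because neither route fully handles loss that depends on depression at 12 months.

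The cost is a change of wording and slightly more analysis work. No new data and no additional participants are needed.
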